### Study Procedures

Figure 2 illustrates the study enrollment procedure. After obtaining informed consent, pediatric patients will be randomly assigned to either a VR app group, which will undergo amblyopia treatment using the VR app for pediatric patients with amblyopia combined with full refractive correction glasses, or a control group, which will undergo amblyopia treatment based on occlusion treatment with an eye patch combined with full refractive correction glasses [24]. Patients assigned to the VR app group will use the VR app for amblyopia at home for 1 hour per day for 6 months, in combination with full refractive correction glasses. Patients assigned to the control group will follow occlusion therapy with an eye patch for 6 months, also wearing full refractive correction glasses, and the duration of eye patch use will be determined by the prescribing physician. Both groups underwent ophthalmological examinations on the first day of the trial and at weeks 4, 8, 12, 16, 20, and 24. Ophthalmological examinations will include measurements of visual acuity, intraocular pressure, strabismus angle, stereopsis, refractive error, and corneal curvature. Only the VR app group will perform a digital stereopsis test using the VR app once per week and complete a usability questionnaire on the VR app at weeks 2, 12, and 24. The week 2 visit conducted only for the VR app group is intended to confirm that the study participants, particularly those unfamiliar with VR devices, are using the VR app correctly and facilitate their continued appropriate use. Only the control group will record their daily duration of eye patch use in a diary. Study participation will end for both groups after the 24-week visit.

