To evaluate the effects of amblyopia treatment in the control and VR app groups, BCVA in the amblyopic eye will be assessed as secondary outcome 1 and stereopsis in the amblyopic eye as secondary outcome 2. To assess the reliability and validity of stereopsis measurement using the VR app, secondary outcome 3 will involve comparing stereopsis in the amblyopic eye measured using the VR app for pediatric amblyopia with that obtained during clinical visits using the Titmus stereo test. To evaluate treatment adherence in the control and VR app groups, secondary outcome 4 will involve assessing the ratio of the total wearing time to the target wearing time. To evaluate the safety of amblyopia treatment using the VR app, secondary outcome 5 will involve comparing the angle of strabismus in the amblyopic eye between the control and the VR app groups. To investigate how VR gameplay status correlates with efficacy and safety, secondary outcome 6 will involve examining the VR gameplay status in the VR app group (including game type, play date or time, play duration, and game settings) in relation to BCVA, stereopsis, treatment adherence, and ocular deviation. Secondary outcome 7 will evaluate malfunctions of the VR app for pediatric amblyopia, secondary outcome 8 will monitor adverse events, and secondary outcome 9 will assess usability in the VR app group. Adverse events will be monitored throughout the trial. Based on our safety evaluation of the VR app in adults, where no visually induced motion sickness (VIMS) or vision-related adverse events occurred [18], the intervention is not expected to pose major safety concerns. However, careful monitoring remains essential in pediatric populations. Possible adverse events include VIMS, asthenopia, diplopia, transient blurring, and headaches. All adverse events reported by participants or observed during clinic visits will be documented and evaluated for severity and relationship with the intervention. Among the secondary outcomes, those related to BCVA, stereopsis, ocular deviation, and treatment adherence (secondary outcomes 1‐4) have been defined as key secondary end points. Since this is an exploratory clinical study, all secondary outcomes other than the primary outcome will be analyzed and interpreted in an exploratory (hypothesis-generating) manner.

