For between-group comparisons of BCVA, stereopsis, ocular deviation, and the ratio of total treatment time to the target treatment time, 2-tailed *t* tests or repeated-measures mixed-effects models will be used. Within-group comparisons will be conducted with 2-tailed paired *t* tests, repeated-measures analysis of variance, or repeated-measures mixed-effects models. Reliability and validity evaluations of stereopsis measurements using the VR app compared with the Titmus stereo test administered at clinical visits will be performed using 2-tailed paired *t* tests, Cronbach α coefficients, or intraclass correlation coefficients. The associations between VR gameplay status, ophthalmological examination results, and treatment adherence will be examined using multiple regression analyses or mixed-effects models adjusted for confounding factors. The number of adverse events in the control and VR app groups will be compared using the chi-square test. If continuous variables deviate substantially from a normal distribution, more appropriate methods such as the Mann-Whitney *U* test will be applied. A 2-sided significance level of 5% (*P*<.05) and 95% CI will be used for all analyses. We will not apply multiplicity adjustments across secondary outcomes that represent different endpoint domains. However, when repeated measurements of the same outcome are compared at multiple time points (eg, longitudinal analyses of BCVA), appropriate multiple-comparison adjustments (eg, Bonferroni correction or equivalent family-wise error control) will be applied within that end point family. Primary and secondary analyses will follow intention-to-treat, including all data collected before withdrawal. A per-protocol analysis will be performed as supplementary to assess the robustness of the findings.

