This study has certain limitations. First, despite the explicit inclusion criteria specifying participants with anisometropic, strabismic, or refractive amblyopia and a BCVA of ≤0.5 logMAR in the amblyopic eye, heterogeneity in disease severity, underlying etiology, and associated comorbidities may influence therapeutic outcomes. Second, interindividual differences in age, prior exposure to VR devices, and degree of familiarity may have affected both adherence and therapeutic response, especially during the initial phase of the study. To minimize the influence of such heterogeneity, participants allocated to the VR app group underwent an interim visit at week 2—prior to the first ophthalmologic assessment at week 4—during which VR app usage was reviewed to facilitate the proper continuation of treatment, even among participants with limited prior experience using VR systems. Third, the extended use of the VR app carries the potential risk of adverse effects, including VIMS and asthenopia. Our prior safety evaluation of the VR app in adults revealed no VIMS- or vision-related adverse events [18]. However, data on the long-term use of VR apps in pediatric populations remain limited, and the occurrence of adverse events could potentially affect treatment adherence and diminish the therapeutic efficacy of amblyopia management. Fourth, while amblyopia therapy in clinical settings is generally expected to extend beyond the 6-month duration of this study, this protocol does not permit the evaluation of long-term efficacy, posttreatment sustainability of therapeutic benefits, or the risk of amblyopia recurrence. Upon the completion of this study, an extension study is being conducted to allow interested participants to continue treatment with the VR app. The implementation of such a study with an extended follow-up would facilitate the assessment of long-term therapeutic efficacy and safety, persistence of treatment effects, and the likelihood of amblyopia recurrence. Fifth, the VR app–based stereopsis test used here was newly developed without formal validation. From a visual psychophysics perspective, this task uses a 4-alternative forced-choice design with size-constancy adjustments to reduce monocular cues. However, the extent of monocular cue elimination remains unverified. The floor and ceiling disparity levels of this stereotest are undetermined. Therefore, the stereopsis outcomes should be interpreted as preliminary. We included an in-headset stereopsis measure as it may provide a practical way to assess stereopsis under intervention conditions and enable monitoring between clinic visits, with potential utility for future clinical implementation and remote assessment in telemedicine.

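### The VR arm alone has a week-2 visit, so comparing the number of adverse events between arms could show somewhat more events on VR even if true harm is equal

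*Protocol article*

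**What the plan says.** Capture of events is described under Secondary Outcomes: "All adverse events reported by participants or observed during clinic visits will be documented and evaluated for severity and relationship with the intervention". The same section adds that "Adverse events will be monitored throughout the trial". There are therefore two routes into the record, spontaneous report and clinic visit.

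The visit schedule is under Study Procedures. For the shared visits: "Both groups underwent ophthalmological examinations on the first day of the trial and at weeks 4, 8, 12, 16, 20, and 24". For the extra one: "The week 2 visit conducted only for the VR app group is intended to confirm that the study participants" are using the app correctly. The Discussion confirms it: "participants allocated to the VR app group underwent an interim visit at week 2", ahead of the first ophthalmologic assessment at week 4. VR families also "complete a usability questionnaire on the VR app at weeks 2, 12, and 24". The control arm has no matching week-2 contact. Its own additional record is a patch-time diary ("Only the control group will record their daily duration of eye patch use in a diary"), and symptoms are not mentioned as a diary item.

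The between-arm analysis is under Sample Size and Statistical Analyses: "The number of adverse events in the control and VR app groups will be compared using the chi-square test". Nothing there or elsewhere in the article allows for the unequal schedule. The Discussion presents the week-2 visit only as a way to reduce differences in familiarity with VR.

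**The concern.** A count of adverse events measures both how much harm occurred and how often someone was in a position to record it. Here the second part differs by arm. The difference falls in the first month, when symptoms from starting to use a headset would also be looked for. The possible events that the article lists include several short-lived symptoms that depend on being mentioned: motion sickness, eye strain, transient blurring and headache. The children are 3 to 10 years old. A symptom in week 1 that has gone by week 2 is more likely to be mentioned at a visit one week later than at a visit three weeks later.

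The trial is open-label, so masking does not even out reporting. The article itself says that careful monitoring is essential in children and that long-term paediatric data are limited. An early VR excess could then be misread in either direction: a visit artefact taken for harm, or real harm explained away as a visit artefact.

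This is more than missing detail. The article itself fixes the capture routes, the schedule and the between-arm comparison, and the three do not fit together.

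**Working it through.** The article gives no event rate, recall figure or expected count, so there is no stated figure to reproduce. The check has two parts: a count taken from the text, and a model that rests on assumptions.

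**Count (from Study Procedures)**
- VR, post-baseline: weeks 2, 4, 8, 12, 16, 20, 24 = 7 visits.
- Control, post-baseline: weeks 4, 8, 12, 16, 20, 24 = 6 visits.
- Ratio 7/6 = 1.17. In weeks 0-4: 2 against 1.
- Longest wait from onset to the next visit in weeks 0-4: 2 weeks on VR, 4 weeks on control. After week 4 it is the same in both arms.

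**Model (assumptions)**
- True event rates are equal in the two arms.
- An event not reported spontaneously is recorded at the next visit with probability 0.5^(gap/h), where h is the recall half-life in weeks.
- A fraction f of events starts in weeks 0-4; onset is even within weeks 0-4 and within weeks 4-24. Fully even onset over 24 weeks gives f = 4/24 = 1/6.
- A share s is reported spontaneously, whatever the visit schedule.

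The average recording probability over an interval of L weeks is m(L) = (1 − 0.5^(L/h)) / (L·ln2/h). Control records c = m(4) throughout. VR records v = f·m(2) + (1 − f)·m(4). The ratio of recorded events is [s + (1 − s)v] / [s + (1 − s)c].

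Worked example, h = 1, f = 1/6, s = 0: m(2) = 0.541, m(4) = 0.338, v = 0.541/6 + 0.338 × 5/6 = 0.372, ratio 0.372/0.338 = 1.10.

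VR/control ratio over 24 weeks:

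| h (weeks) | m(2) | m(4) | f = 1/6, s = 0 | f = 1/3, s = 0 | f = 1/2, s = 0 | f = 1/6, s = 0.5 | f = 1/2, s = 0.5 |
|---|---|---|---|---|---|---|---|
| 0.5 | 0.338 | 0.180 | 1.15 | 1.29 | 1.44 | 1.02 | 1.07 |
| 1 | 0.541 | 0.338 | 1.10 | 1.20 | 1.30 | 1.02 | 1.08 |
| 2 | 0.721 | 0.541 | 1.06 | 1.11 | 1.17 | 1.02 | 1.06 |
| 4 | 0.845 | 0.721 | 1.03 | 1.06 | 1.09 | 1.01 | 1.04 |

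With s = 1, or with perfect recall, every entry is 1.00. No entry can be below 1, because m(2) is at least m(4). Within weeks 0-4 alone the ratio at s = 0 is m(2)/m(4), from 1.88 (h = 0.5) down to 1.17 (h = 4).

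**Effect on the test.** This was computed exactly for an uncorrected chi-square on children with at least one recorded event, 15 per arm, two-sided 5%. The assumptions were half of events in weeks 0-4, no spontaneous reporting, 0.5 to 2 true events per child, and recall decaying as exp(−gap/τ) with τ of 1 to 4 weeks. The chance of a significant result with VR worse is about 3.7% to 7.8%, against 1.5% to 2.8% if capture were equal.

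**After the change.** If the comparison uses ascertainment common to both arms (6 visits against 6, plus spontaneous reports), the expected ratio under equal true harm is 1.00, provided that the week-2 contact does not itself change what VR families report elsewhere.

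**The case against.** The strongest reply is that the larger ratios need one of the two capture routes to be switched off. The article allows events to be reported by participants and says that monitoring runs throughout the trial. If half of events arrive that way, the excess shrinks to about 1% to 8%. The 1.44 figure also needs very heavy loss: at h = 0.5 the control arm misses 1 − 0.180 = 82% of its events, and nothing in the article suggests that. This stands. The upper figures are the edge of an assumed range and not an expectation.

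Second, the outcome carries limited weight. Adverse events are secondary outcome 8, outside the key secondary endpoints, and all secondary outcomes are declared exploratory. Each event is also judged for its relationship with the intervention, and the bias runs against the new device, so it would not hide harm. This also stands and lowers the importance. Exploratory status does not, however, remove a bias whose direction is known.

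Third, a common symptom query at each visit may exist in the full protocol or the case report form, and the article does not say that events are actively asked about at week 2. That is fair. But week 2 is a visit, visits are a stated capture route, and nothing in the article equalises the arms.

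A reader might infer more than the documents support, in three ways:
- That equal harm will necessarily be recorded as more events on VR. It will not if recall or spontaneous reporting is complete.
- That the share of VR events first recorded at week 2 measures the bias. It does not, since many of those events would have been recorded at week 4 anyway; only the ratio measures excess.
- That artefact and effect can never be separated. If events are dated or tied to a visit, a sensitivity analysis can set the week-2 records aside.

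**Conclusion.** The point holds in conditional form. It is certain from the text that visit-based ascertainment is unequal (7 visits against 6; 2 against 1 in weeks 0-4) and that the planned comparison ignores this. It is also certain that any resulting bias is toward more recorded events on VR, concentrated in the first month.

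The size is not known from the document. It depends on recall, on the timing of onset and above all on how much is reported between visits. Plausible values run from no excess to a few per cent with substantial spontaneous reporting, and to 3% to 15% with none and even onset. Figures up to 44% need fast forgetting, no spontaneous reporting and front-loaded events together. Even under front-loaded onset with no spontaneous reporting, the chance of a spurious VR-worse test result stays below 8%.

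For an exploratory safety comparison in 30 children this is a minor to moderate point. It is worth correcting because the remedy is cheap.

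**What to change.** Under Secondary Outcomes, state that at each shared visit (weeks 4, 8, 12, 16, 20 and 24) both arms are asked the same symptom question, covering the whole interval since the previous shared visit. At week 4 it covers weeks 0-4 in both arms, whatever was said at week 2.

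Under Sample Size and Statistical Analyses, base the between-arm comparison on events recorded at shared visits plus events reported between visits in either arm. Leave out only events found solely at the VR-only week-2 visit. Restricting the comparison to shared-visit records alone would be too narrow, because it would also drop spontaneous reports in both arms. Document the week-2-only events in full, list them separately as VR-arm safety data, and show the comparison with all events alongside.

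The cost is one form item and one extra analysis, with no added visit or participant. The downside is that week-2-only VR events are missing from one of the two comparisons. Some asymmetry may remain: VR families may be prompted by the week-2 conversation, or may not repeat at week 4 what they have already reported. The report should say so.

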**Methods:**

This is a multicenter, open-label, prospective, randomized controlled trial that will be conducted at 3 centers in Tokyo, Japan. Pediatric patients aged 3-10 years with anisometropic, strabismic, or refractive amblyopia will be enrolled. Participants will be assigned 1:1 to a VR app group or a control group. The VR app group will use the VR app at home for 1 hour per day for 6 months. The control group will undergo conventional occlusion therapy with an eye patch for 6 months. Each group will comprise 15 participants (30 participants in total). Ophthalmologic examinations will be performed at baseline and at weeks 4, 8, 12, 16, 20, and 24. The primary endpoint will be the change in the best-corrected visual acuity in the amblyopic eye from baseline to week 12. Secondary endpoints will include changes in best-corrected visual acuity, stereopsis, and ocular deviation through week 24. We will also assess treatment adherence, defined as the ratio of the cumulative actual treatment time to the cumulative prescribed time; record adverse events, and evaluate usability in the VR app group. Longitudinal changes in outcome measures will be analyzed using a mixed-effects model.

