### Sample Size and Statistical Analyses

The primary outcome of this study will be to determine whether the improvement in BCVA from enrollment to 12 weeks in the VR app group is noninferior to the improvement in BCVA from enrollment to 12 weeks in the control group. Based on the assumption that the difference in mean BCVA at 12 weeks between the control and VR app groups will be 0.07 LogMAR [35], the common standard deviation will be 0.14 [36] LogMAR, the noninferiority margin will be 0.10 LogMAR [37], the significance level will be 2.5%, and statistical power will be 90%, a sample size of 24 participants (12 per group) is required [19]. Anticipating a dropout rate of approximately 20%, the target sample size has been set to 30 participants (15 per group).

To assess whether the VR-based program for amblyopia is noninferior to eye patch therapy, the 95% CI for the change in BCVA between 0 and 12 weeks will be calculated for both the control and VR app groups. If the lower bound of the 95% CI for the change in BCVA in the VR app group is greater than that in the control group, the VR-based program for amblyopia will be considered noninferior to eye patch therapy, and the primary outcome criterion will be met.

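### The adverse-event comparison is a chi-square on the number of events, so repeated events in one child count as independent and the 5% test can reject too often

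*Protocol article*

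**What the plan says.** Under Sample Size and Statistical Analyses, one sentence covers adverse events: "The number of adverse events in the control and VR app groups will be compared using the chi-square test". The threshold comes from the same section ("A 2-sided significance level of 5"%, applied to all analyses). No alternative test is named for this comparison. The section's only fallback is for continuous variables that are far from normal.

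Under Secondary Outcomes, adverse events are to be monitored for the whole trial and every one documented. The section gives examples: "Possible adverse events include VIMS, asthenopia, diplopia, transient blurring, and headaches". It also makes all secondary outcomes exploratory. Participation ends at week 24 (Study Procedures), and the target is 15 children per group.

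**The concern.** A chi-square test needs independent observations. The symptoms listed are ones that a child could report more than once in six months, and some children are likely to be more prone to them than others. That is a reading of the list; the article does not say that events recur. If they do, event totals vary more between arms than the test assumes, and a few symptomatic children can produce a nominally significant difference in either direction.

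The sentence also leaves the table undefined. Event totals have no natural denominator, and a two-by-two table with 15 children per row cannot be filled once an arm has more than 15 events.

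At stake is a misleading P value in the only test stated for adverse events. The trial concerns children aged 3 to 10, for whom the Discussion says that long-term data on VR apps are limited.

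**Working it through.** **Inputs from the article:** 1:1 allocation, 15 children per group, two-sided 5%, events counted over the whole trial. It states no adverse-event rate, dispersion or power, so there is no figure of its own to reproduce here. **Assumptions:** mean events per child μ from 0.1 to 2, dispersion k from 2 to 0.5, equal follow-up, and no true difference.

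**1. One-child illustration.** With equal arms and event totals a and b, the one-degree-of-freedom statistic is (a − b)²/(a + b), compared with 3.84. Suppose one child reports four headaches and no other child reports anything. Then (4 − 0)²/(4 + 0) = 4.0, P = .046. One child is enough.

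**2. Error rate on event totals.** If counts per child are negative binomial with variance μ + μ²/k, an arm's total over 15 children is negative binomial with mean 15μ and dispersion 15k. The rejection probability can therefore be summed exactly:

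| Mean events per child | No clustering (Poisson) | k = 2 | k = 1 | k = 0.5 |
|---|---|---|---|---|
| 0.1 | 3.0% | 3.3% | 3.7% | 4.4% |
| 0.2 | 4.7% | 5.6% | 6.6% | 8.5% |
| 0.5 | 4.7% | 7.5% | 10.3% | 15.6% |
| 1 | 5.2% | 11.1% | 16.6% | 25.5% |
| 2 | 5.0% | 16.4% | 25.5% | 37.6% |

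As a check, the variance is inflated by 1 + μ/k, so the approximate error is 2[1 − Φ(1.96/√(1 + μ/k))]. For μ = 2 and k = 1 the inflation is 3, and 1.96/√3 = 1.13 gives about 26%, in line with the table. Simulation with 200,000 trials per setting agrees.

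**3. Is the sample size to blame?** Change the unit to children with at least one event, 15 per arm, and enumerate all tables. Pearson's type I error is 0.5%, 2.5%, 5.0%, 5.5%, 4.9% and 4.6% at risks of 5%, 10%, 20%, 30%, 40% and 50%. The maximum is 5.5%, or 6.4% if only 12 per arm remain. For rare events the test is conservative. Fisher's exact test at 15 per arm has a maximum of 1.8%.

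**4. Power at child level, 15 per arm.** With risks of 40% v 6.7%, Pearson has 63% and Fisher 45%. With 30% v 5%, the figures are 45% and 27%.

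**The case against.** **The sentence may be loose wording for children with events.** A conventional chi-square compares groups of people, so this is plausible, and the statistic in step 1 is one way to carry out an event-level test that the article does not spell out. But the two readings are different analyses and can disagree. As written, the independent analyst would have to choose between them.

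**Event rates may be low.** The article reports no motion sickness or vision-related events in its adult evaluation and expects no major safety concern. At 0.1 events per child the test stays below 5% even with strong clustering. This stands: the size of the problem depends on inputs the article does not give.

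**The comparison is exploratory.** This also stands. Adverse events are outside the key secondary endpoints, and the article ties no success or stopping decision to this P value.

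Two stronger readings are tempting and are not supported:

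- A reader might infer that 15 per arm itself makes chi-square give false safety signals. Expected cell counts do fall below 5 when 9 or fewer of the 30 children are affected, and single tables can split the tests (4/15 v 0/15: Pearson P = .03, Fisher P = .10). Step 3 shows no material inflation; such tables largely reflect Fisher's conservatism. At child level, one, two or three affected children against none give Pearson P = .31, .14 and .07.
- A reader might infer that this is the trial's only safety comparison. Secondary Outcomes also compares the angle of strabismus between groups as a safety measure, and each event is to be judged for severity and relation to treatment.

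**Conclusion.** The point holds for the unit of analysis. Followed as written, the rule tests event counts as if independent, and it can reject too often when events cluster within children. Under the assumed rates and dispersions the error runs from under 5% at 0.1 events per child to about 38% at a mean of 2 with k = 0.5. Without clustering it is about 5% or less. The inflation comes from counting events, not from the number of children. Because the comparison is exploratory, this is a correction to the wording of the analysis and does not threaten the trial's main conclusion.

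**What to change.** Replace the sentence so that the comparison is of the number of children with at least one adverse event, overall and by type. Lead with the risk difference and an exact or other small-sample 95% CI. If a P value is given, name the small-sample test in advance. Report total events descriptively per child-week, or with a rate model that allows for within-child clustering and exposure time.

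The change takes a sentence or two and leaves design and data collection as they are. It has two costs. Collapsing repeated events to one per child loses information, which the descriptive totals partly restore. If Fisher's exact test is chosen, the loss of power is material (63% to 45% in the first case of step 4). That matters where a missed safety signal is a concern, so the interval should carry the interpretation. Fisher over Pearson at child level is largely a matter of preference; what matters is the unit and that the choice is stated.

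### The one between-arm adverse-event comparison stated is an undivided event count, which with 15 children per arm can dilute an excess of the headset symptoms the protocol names

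*Protocol article*

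**What the plan says.** In the protocol article, Sample Size and Statistical Analyses gives one sentence on the analysis of adverse events: "The number of adverse events in the control and VR app groups will be compared" by a chi-square test. It gives no event type, no restriction by severity or relationship, and no unit (events or children). The same section sets a two-sided 5% level for all analyses.

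Secondary Outcomes lists what is expected: "Possible adverse events include VIMS, asthenopia, diplopia, transient blurring, and headaches", where VIMS is visually induced motion sickness. It also states that "All adverse events reported by participants or observed during clinic visits will be documented and evaluated for severity and relationship with the intervention". The limitations paragraph of the Discussion returns to the subject: "the extended use of the VR app carries the potential risk of adverse effects, including VIMS and asthenopia". It adds that data on long-term use in children are limited; the earlier safety evaluation was in adults.

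Two further statements bear on the point. A separate safety comparison is planned: "To evaluate the safety of amblyopia treatment using the VR app, secondary outcome 5 will involve comparing the angle of strabismus" between the groups. And "all secondary outcomes other than the primary outcome will be analyzed and interpreted in an exploratory (hypothesis-generating) manner", which covers adverse events (secondary outcome 8).

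**The concern.** The stated comparison does not fit the safety question that the article itself sets. That question is whether children using a headset daily for six months get motion sickness, eye strain, double vision, blurring or headache. An undivided count adds those symptoms in one arm to whatever the patch causes in the other and to ordinary childhood illness in both. Similar counts in the two arms then say little about the named symptoms, and the type and relationship recorded for each event go unused in the comparison.

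This is separate from the undefined unit. Counting children instead of events, or using an exact test, would not remove the dilution as long as all event types are combined. At stake is the trial's information on tolerability in children, where the article says evidence is thin.

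**Working it through.** **Inputs from the article.** 15 children per group (24 / 0.8 = 30 in total after the 20% dropout allowance); two-sided 5% level; chi-square test. The article gives no adverse-event rate, power or sample size, so there is no safety figure of the plan's to reproduce.

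**Assumed inputs.** Named-symptom rate v in the VR arm and c in the control arm; background-illness rate b in both arms; patch-related event rate p in controls. Events are taken as independent and counted per child. The plan does not fix the unit, and the per-child reading is the one under which a chi-square test is valid.

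**Formulas.** Probability of any event:
- VR arm: 1 − (1 − v)(1 − b)
- control arm: 1 − (1 − c)(1 − b)(1 − p)

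Power is the sum of the binomial probabilities of all pairs of counts (0 to 15 in each arm) for which the test gives P < .05. The chi-square is uncorrected.

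**Named symptoms only, v = 40%**

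| Control rate c | Fisher | Chi-square |
|---|---|---|
| 0% | 0.78 | 0.91 |
| 2% | 0.67 | 0.82 |
| 10% | 0.33 | 0.51 |

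**Any event, same harm (v = 40%, c = 0%), chi-square**

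| Background b | Patch p | Any event, VR | Any event, control | Power |
|---|---|---|---|---|
| 20% | 0% | 1 − 0.6 × 0.8 = 52% | 20% | 0.46 |
| 40% | 0% | 1 − 0.6 × 0.6 = 64% | 40% | 0.25 |
| 40% | 20% | 64% | 1 − 0.6 × 0.8 = 52% | 0.10 |
| 40% | 40% | 64% | 1 − 0.6 × 0.6 = 64% | 0.05 |

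Setting a pooled chi-square against Fisher's test understates the loss, because Fisher is the more conservative of the two. With the chi-square throughout, the fall at c = 0% is from 0.91 to 0.46 or 0.25. At c = 10% and b = 20%, the any-event rates are 52% and 1 − 0.9 × 0.8 = 28%, and chi-square power falls from 0.51 to 0.26. Dilution remains, but the type-specific test is then weak as well.

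**Lower harm rate.** With v = 30% and c = 2%, the type-specific chi-square has power 0.59 (Fisher 0.39). The any-event chi-square has 0.27 at b = 20% and 0.14 at b = 40%, with no patch events.

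**One possible trial.** Named symptoms in 6/15 against 0/15: chi-square = 30 × (6 × 15 − 9 × 0)² / (15 × 15 × 6 × 24) = 7.5, P = .006; Fisher P = .017. Any event in the same children, 10/15 against 9/15: chi-square = 30 × (10 × 6 − 5 × 9)² / (15 × 15 × 19 × 11) = 0.14, P = .70.

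**What an interval would show.** If none of 15 VR children has a named symptom, the exact two-sided 95% upper limit is 1 − 0.025^(1/15) = 21.8%. A P value on the overall count conveys nothing of this.

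**The case against.** The strongest reply is that this is a condensed article. The sentence names a test and does not claim to list every adverse-event summary. Tables by type, severity and relationship are routine content of an analysis plan, and that plan is not shown. The article already commits to grading each event, so headset-related events would be identified one by one. Safety also has another measure, the strabismus angle, and the outcome is exploratory.

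Much of this stands. The absence of such tables from the article is not a finding. A reader might infer that the overall count is the only adverse-event summary, that no rate of any named symptom will be produced, or that a nonsignificant result will be taken as evidence of safety. The article says none of these things. It does not describe the count as total or as the sole analysis, and it stresses careful monitoring in children.

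What does not fall away is the choice that is stated. The article picks one comparison for adverse events, and that comparison uses neither the named symptoms nor the grading. The strabismus angle does not capture those symptoms. Exploratory status favours estimates by type over a single P value.

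The figures also deserve caution. The row with power 0.05 is built in: once patch-related events are as common as headset symptoms, the two overall rates are equal and any test rejects at about its nominal level. The article names no patch-related event. The argument therefore rests on the rows with background illness alone.

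**Conclusion.** The point holds in a limited form. The only between-arm adverse-event comparison that the article states is an undivided count. Read naturally, it pools all events, and at 15 children per arm it can dilute an excess of the named symptoms. For a 40% against 0% excess, power is about 0.46 or 0.25 (background 20% or 40%, no patch events), against 0.78 for Fisher's test on those symptoms. The advantage shrinks as controls share the symptoms: Fisher's power is 0.67 at 2% and 0.33 at 10%.

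These figures illustrate a property of pooling under assumed, independent per-child rates. They do not measure a defect known to occur in this trial. A misleading report of no difference is possible but does not follow from the text, because descriptive tables may be planned elsewhere. The matter is worth correcting because the better summary uses data already being collected.

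**What to change.** In Sample Size and Statistical Analyses, replace the event-count chi-square as the stated safety comparison. For each arm, report:

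- the number and percentage of children with at least one of VIMS, asthenopia, diplopia, transient blurring or headache, for each symptom and as a composite;
- the number and percentage with at least one event judged related to treatment;
- an exact 95% confidence interval for each percentage, and the risk difference between arms.

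Present these descriptively, and keep the count of all events as description only.

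The cost is a change of wording and one table from information already recorded. The downside is several estimates from small counts with wide intervals: 6 of 15 gives an exact 95% interval of about 16% to 68%. That width is the honest statement of what 15 children per arm can show.
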